##### Anthropometry

We will measure all students’ height and weight, using stadiometers (Surgical and Medical Products No. 26SM, Medtone Education Supplies, Melbourne, Australia) and digital scales (UC-321, A&D Company LTD, Tokyo, Japan), respectively. We will then calculate body mass index (BMI) and BMI z-scores using the Centers for Disease Control and Prevention methodology [47].

##### Student characteristics

Students will self-report their sex and date of birth. They will also indicate the country in which they were born and the language they speak at home. We will use this information to categorize students into one of seven ethnic backgrounds (English, European, Middle Eastern, Asian, African, South Pacific or ‘other’), based on the Australian Bureau of Statistics’ Standard Classification of Languages [48]. We will also ask students to indicate if they are of Indigenous origin (i.e., Aboriginal or Torres Strait Islander). We will assess student-level socioeconomic status through the child’s self-reported home suburb, children’s perception of the number of books in their home (as measured in Trends in International Mathematics and Science Study) [49], and a single-item question on perceived socioeconomic status [50].

##### Student physical activity (self-report)

We will measure students’ activity behaviors using single item measures of (i) typical physical activity participation [51], (ii) physical activity participation last week [51], (iii) organized sport participation in the past year with team and individual sports measured separately [52] and (iv) active commuting to school [52].

##### Teachers’ interpersonal style during PE and school sport

We will use a 4-item scale to assess students’ perceptions of their teacher’s support of students’ psychological needs. This will involve two items from an adapted version of the Teacher as Social Context questionnaire [53], one item adapted from the Health Care Climate Questionnaire [54] and one item from the Controlling Teacher Scale [55].

##### Student behavior, affect and cognition during PE and school sport

We will assess effort through three items, including two items from the Student Engagement in School questionnaire [56] and one item from the effort subscale of the Intrinsic Motivation Inventory [57]. *Enjoyment* will be assessed using three items adapted to PE and school sport from the Student Engagement in School questionnaire. Three items will be used to assess students’ concentration in the lessons [58]. Three items from the *Use of Strategies* subscale of the Cognitive Processes Questionnaire in Physical Education [59] will measure strategies students employ when learning in PE and school sport.

##### Subjective well-being

We will measure students’ perceived well-being using 10 items from the WHO’s Health Behavior in School-aged Children questionnaire [50].

##### Academic achievement

We will work with NSW BOSTES to obtain students’ Year 3 and 5 NAPLAN numeracy and literacy standardized test scores [60].

### Student level measures – sub-sample

Within each school, we will randomly select one class to form a sub-sample. We expect 18 students per class to volunteer; therefore, the subsample will include approximately 360 children. Children in the sub-sample will complete the following measures in addition to the previously described measures.

#### Fundamental movement skill competency

Students’ fundamental movement skill competence will be measured using three object-control skills from the Test of Gross Motor Development-2 [61]. From the 12 skills available, we selected the overarm throw, catch, and kick due to their transferability into a variety of different sports that are popular among Australian children. Moreover, object control skills are most strongly associated with physical activity levels in comparison to locomotor and stability skills [62, 63].

#### Cognitive control

We will measure children’s working memory and inhibition using a modified AX-Continuous Performance Task (AX-CPT) [64]. The tests will be administered by trained research assistants and completed by participants using a computer. The AX-CPT requires participants to correctly respond to target trials that occur when the letter ‘X’ (correct-probe) is immediately preceded by the letter’A’ (correct-cue). Non-target trials occur when probes are letters other than X (collectively referred to as’Y’) and/or cues are letters other than A (referred to collectively as’B’). Thus, participants encounter four types of trials: AX, AY, BX, and BY [65].

### Principal level measures – entire sample (online questionnaires)

#### Principal characteristics

Principals will self-report their demographic information (age, sex, ethnicity, and number of years teaching). Additionally, we will ask principals to declare if they have ever been accredited as a specialist PE teacher, and to self-report their physical activity [51] and sport participation [52].

#### School characteristics

Principals will complete items measuring the number of classes, number of students per class, number of employed teaching staff within their schools, number of PE specialist teachers and bell times for the school (e.g., school start, recess, lunch, and school end times).

#### School physical activity

We will assess principals’ perceptions of facilities, equipment, time allocation, and support for physical education in their school using 13 items from the NSW School Physical Activity and Nutrition Survey [66]. A single-item measure will be used to determine if schools currently receive ‘*Sporting Schools*’ funding for external providers to run sport programs within the school.

### Teacher level measures– entire sample (online questionnaires)

#### Teacher characteristics

As with principals, teachers will self-report their demographic information (date of birth, sex, ethnicity, and number of years teaching). We will also ask teachers to report the stage they are currently teaching, and their current level of BOSTES accreditation. Additionally, we will ask teachers to declare if they have ever been accredited as a specialist PE teacher, and to self-report their physical activity [51] and sport participation [52].

#### Teacher confidence

We will assess teacher confidence in teaching PE and school sport, as well as other key learning areas (e.g., English, Mathematics, Science and Technology), by adapting a measure of non-specialist primary teachers’ confidence to teach PE [67].

#### Student conduct

A single item measure will be used to assess teachers’ perceptions of their students’ behavior [56].

#### Perceived student engagement

We will measure teachers’ perception of their students’ engagement in PE and school sport lessons, as well as other key learning areas (e.g., English, Mathematics, Science and Technology) using an adapted version of the Student Engagement in School Questionnaire [56].

#### Internet self-efficacy

An eight-item Internet self-efficacy scale will be used to assess teachers’ beliefs in their ability to utilize internet tools [68].

#### Job satisfaction, burnout and absenteeism

Single-item measure of overall job satisfaction [69] and burnout [70] will be used. Additionally, we will seek permission from teachers to collect from their principal the number of days absent from work due to illness.

##### Statistical analyses and sample size

We will test for between-arm differences in changes in student outcomes using linear mixed models with standard errors corrected for clustering. We will analyze data according to intention to treat principles (main analyses) and per-protocol principles (sensitivity analyses). We conducted a power analysis using procedures appropriate for complex nested designs [71]. In this analysis the effect size for between-arm differences in cardiorespiratory fitness (primary outcome) was conservatively set to .35 (note: effect in our efficacy trial was .54) with intraclass correlations based on our efficacy trial [21] (class = .09, school = .01). Analysis indicated that 1080 students from 60 classes in 20 schools (i.e., 3 classes per school) would provide power of .91.

We will explore potential moderators of intervention effects including children’s age, sex, ethnicity, weight status and SES, as well as baseline levels of cardio-respiratory fitness, physical activity and fundamental movement skill competence. As with the main analyses, we will employ a mixed modeling approach to explore moderation hypotheses by including appropriate interaction terms in the regression models. The trial is not powered to detect interactions; thus, we will employ a significance level of *p* < 0.1 to explore potential moderators. We will explore significant interaction terms by testing sub-groups differences on the primary outcome and selected secondary outcomes. We will also explore potential moderating effects of principal and teacher characteristics (e.g., specialist PE accreditation) on student outcomes.

Per protocol analyses will investigate the influence of *iPLAY* leaders’ and other teachers’ adoption and implementation of the intervention on student outcomes. Adoption will focus on the proportion of intervention training components completed (e.g., workshops attended and online tasks completed), while implementation will evaluate leaders’ and teachers’ utilization of strategies in their schools (as per Table 1).

Linear mixed models will be also used to examine potential mediating processes. For example, in our efficacy study we found that changes in fundamental movement skills mediated the effect of the intervention on children’s physical activity and cardiorespiratory fitness. Mediating effects will be estimated using a cluster-bootstrapped based product-of-coefficients test that is appropriate for cluster RCTs.

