From within each cohort, we will select 10 schools to participate in the cluster RCT; the other 80 schools will participate in the scale-up implementation study. Selecting schools for the cluster RCT will involve a four-step approach. The aims of this process are to ensure that schools in the cluster RCT are: (i) broadly representative of schools in NSW and (ii) assigned to trial arms such that most school-level covariates (e.g., socioeconomic status [SES], geographic location) are balanced, thereby increasing the likelihood that children in the two conditions are similar on the outcome variables at baseline. The four steps are:*Stratification:* All schools that express interest in the study and are among the 90 selected to participate in each cohort will be stratified according to SES and geographic location. Given the number of schools is small, the stratification process will require relatively coarse groupings. The Index of Community Socio-educational Advantage (ICSEA) will serve as the SES variable. This index includes information regarding parental SES and Indigenous representation [33]. The index has a median of 1000 and ranges Australia-wide from 300 to 1300 indicating heavy negative skew [33]. NSW has a similar distribution ranging from 582 to 1202 with a median of 1003. We will split the sample into a higher SES stratum (ICSEA < =1003) and a lower SES stratum >1003. These strata will be further split by geographic distribution using the Australian Bureau of Statistics remoteness index by postcode. The index has 12 categories but this will be reduced to two: urban (less remote) and provincial (more remote). This process will produce four strata: (i) urban-higher SES, (ii) urban-lower SES, (iii) provincial-higher SES, and (iv) provincial-lower SES.*Match-pairing:* We will employ a Euclidian distance minimization strategy to create pairs of similar schools from within strata. The variables used in this minimization process will be: (i) ICSEA, (ii) school size (number of students enrolled), (iii) average scores on national standardized test of numeracy and literacy that are completed by all NSW children (see outcomes section for further details) and (iv) school participation (or not) in a state-wide physical activity and nutrition program, known as Live Life Well at School [34], that took place from 2008 to 2015.*Pair selection:* Once schools have been matched using the minimization procedure, we will select the two or three most similar pairs of schools from within each stratum to participate in the cluster RCT. Through this process, four schools will be selected from each of the provincial strata and six schools are chosen from each of the urban strata. This strategy will allow for calculation of average treatment effects and differences in treatment effects by strata.*Randomization*: Following baseline data collection, schools will be randomly assigned from within each pair to the experimental or control arm of the cluster RCT. An experienced statistician who is not part of the research team will conduct the randomization procedure using a computer-generated algorithm.

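### The primary contrast is a difference in changes with no stated adjustment for baseline fitness, which costs precision that a baseline measured before randomization would give free

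*Protocol article*

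**What the plan says.** In the protocol article, under Statistical analyses and sample size, the main analysis reads: "We will test for between-arm differences in changes in student outcomes using linear mixed models with standard errors corrected for clustering". No covariates, fixed effects or random effects are listed. The next paragraph names baseline fitness among possible moderators, to be explored through interaction terms, and gives it no other role.

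Under Recruitment, selection and randomization, the allocation is described in steps. Schools are stratified by SES and location. Then: "We will employ a Euclidian distance minimization strategy to create pairs of similar schools from within strata". After baseline data collection, "schools will be randomly assigned from within each pair to the experimental or control arm of the cluster RCT". The trial's 20 schools come from two cohorts ("From within each cohort, we will select 10 schools to participate in the cluster RCT") and four strata ("four schools will be selected from each of the provincial strata and six schools are chosen from each of the urban strata"). The section adds: "This strategy will allow for calculation of average treatment effects and differences in treatment effects by strata".

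The power calculation uses an effect of 0.35 SD, intraclass correlations of .09 (class) and .01 (school), and 1080 students in 60 classes in 20 schools. It reports power of .91.

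**The concern.** A difference in changes subtracts the whole baseline value from each follow-up value. When baseline and follow-up correlate at less than 1, part of the baseline is noise with respect to follow-up, and full subtraction carries that noise into the treatment estimate. Regression on baseline removes only the part that predicts follow-up.

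This applies to a plain change score and equally to an arm-by-time mixed model with baseline means left free by arm: with complete data the two give the same contrast. At stake is the precision of the primary result. Any chance baseline gap between two groups of only 10 schools is also corrected too far.

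A second question is whether the analysis reflects the strata, cohorts and pairs that restrict the randomization, since the sentence on the model mentions none of them.

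**Working it through.** **1. The plan's own power.** Inputs from Statistical analyses and sample size: effect 0.35, ICCs .09 and .01, 20 schools, 3 classes per school, and 1080/60 = 18 students per class. Two-sided alpha of .05 is assumed.

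Variance = 4 × (.01/20 + .09/60 + .90/1080) = 4 × .002833 = .01133, so SE = .1065 SD.

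0.35/.1065 = 3.288; 3.288 − 1.960 = 1.328; power = .908. This reproduces .91 as an unpaired calculation with a normal approximation. With 18 degrees of freedom for 20 schools the power is .875.

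**2. Change contrast against baseline adjustment.** With equal SDs at both times and correlation r (assumed the same at student, class and school level):

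- variance of change: 2(1 − r)
- variance adjusted for baseline: 1 − r²
- adjusted/change variance ratio: (1 + r)/2
- change/adjusted SE ratio: sqrt(2/(1 + r))

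| r (assumed) | 2(1 − r) | 1 − r² | Variance ratio | SE of change contrast |
|---|---|---|---|---|
| .3 | 1.40 | .91 | .65 | 24% larger |
| .5 | 1.00 | .75 | .75 | 15% larger |
| .7 | .60 | .51 | .85 | 8% larger |
| .8 | .40 | .36 | .90 | 5% larger |
| .9 | .20 | .19 | .95 | 3% larger |

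If 0.35 is in SDs of the outcome itself and the same ICCs apply, normal-approximation power is .794 (change) against .931 (adjusted) at r = .3, .908 against .967 at .5, and .989 against .996 at .7.

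**3. Over-correction.** If the arms differ at baseline by D, the change contrast subtracts D and the adjusted contrast subtracts rD, so the over-correction is (1 − r)D. If baseline has the same variance structure, one standard error of D is .1065 SD. The over-correction is then .5 × .1065 = .053 SD at r = .5, .3 × .1065 = .032 at .7 and .2 × .1065 = .021 at .8. Against an effect of 0.35 these are about 15%, 9% and 6%.

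**4. Leaving out the pairs.** Variance of a school mean = .01 + .09/3 + .90/54 = .0567. School-level matching can remove at most the .01, leaving .0467. The SE is therefore overstated by at most sqrt(.0567/.0467) = 1.10, and the within-pair correlation is at most .01/.0567 = .18.

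Power from 10 pairs on 9 degrees of freedom is .832 if matching explains none of the school variance, .864 if half and .896 if all. A test that ignores the pairs has .875 with no matching gain and about .895 at the ceiling. Simulated type I error of that test is about 4.0% at a within-pair correlation of .1 and 3.1% at .2, below the nominal 5%.

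**5. Strata and cohort as fixed terms.** Four strata use 3 degrees of freedom and two cohorts use 1, so 18 falls to 14. At the SE in step 1, with no precision gain from these terms, power goes from .875 to .863 (noncentral t).

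**The case against.** The strongest reply is that one sentence in a condensed article does not fix a model. A longitudinal mixed model with baseline means constrained equal across arms also estimates a between-arm difference in changes, and it has the full gain from baseline. That is true, so the criticism is conditional: it applies to the two plain readings (change score, or arm-by-time with free baseline means), and the sentence does not exclude them. The figures also rest on an r that the article does not give, and at .8 or above the loss of precision is small. Both readings target the same treatment effect; only the estimator differs.

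A reader might infer more: that the plan ignores pairs, strata and cohorts, and so gives less precise estimates or invalid error bars. The document does not support this.

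- The article is silent on model terms and does not exclude these. Such terms are commonly left to the full plan, and the randomization section foresees effects by stratum.
- With 1:1 allocation in every pair and complete data, the school-level point estimate is the same with or without pair terms.
- The error in the SE is conservative, so it creates no excess of false positives.
- For fitness, a pair term brings essentially no power gain and can lose power.

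Nor can a larger harm be claimed for the matching variables. ICSEA is not an outcome. School test scores are a matching variable and relate to a secondary outcome, but their within-pair correlation is unknown.

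**Conclusion.** The baseline point stands. As worded, the primary contrast carries no stated baseline adjustment. Unless baseline is a covariate or baseline means are constrained, its SE is about 15%, 8% or 5% larger than necessary at r = .5, .7 or .8, and it over-corrects chance baseline differences. This rests on equal SDs at the two times and one r across levels; the size depends on r, but adjustment is the more precise choice for any r below 1.

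On the randomization groups, only a modest point stands: the model should carry the strata and cohorts within which pairs were formed. The pairs themselves can be left out of the primary model at the price of a conservative SE, by at most about 10% for fitness at a school ICC of .01.

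**What to change.** State the primary model as 12-month laps regressed on arm with baseline laps as covariate, fixed terms for the four strata and for cohort, random intercepts for school and class, and small-sample degrees of freedom suited to 20 schools. If 12 and 24 months are modelled jointly, constrain baseline means to be equal across arms instead. Report an analysis with a pair-level term as a sensitivity analysis. Pairs are nested in strata and cohorts, so a pair term there takes the place of both.

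The cost is analysis wording and about 4 degrees of freedom. All the variables are already planned for collection or known from the allocation, and no design change is needed.

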##### Economic evaluation

We will conduct an economic evaluation to determine if *iPLAY* represents ‘value-for-money’ measured incrementally against the attention control arm. This allocative efficiency focus will determine whether the cost of the intervention is justified by the benefits derived from it, measured against usual practice. Costs in each arm of the trial will be estimated from a societal perspective using detailed pathway analysis to identify resource use, measurement and valuation processes for the reference year 2018. The incremental differences in costs will be combined with the behavioral and biophysical outcomes observed in the trial to produce a range of incremental cost effectiveness ratios. In addition to a ‘trial-based evaluation’ (costs and outcomes exactly as per the trial), depending on the outcomes, a modelled economic evaluation with the extended time horizon may be undertaken to further translate the benefits observed in the trial into final health benefits, assessed as disability-adjusted life years (DALYs) averted. The modelled economic evaluation will simulate the impact of increased physical activity and movement skill competency on overall well-being over the lifetime of the cohort compared with usual practice. A Markov model [72] consisting of health states associated with different levels of physical activities/movement skill competency will be used to accrue costs and benefits over the time horizon. The long-term improved outcome may translate into cost savings which offset the increased cost associated with the implementation of *iPLAY* project. Simulation-modelling using the @RISK software package will be used to calculate 95 % uncertainty intervals around the epidemiological probabilities and cost estimates.

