#### Curricular components – classroom teachers

Classroom teachers will participate in professional learning designed to help them implement the curricular intervention components. This training will involve a 2-h workshop (face-to-face), 4 h of online learning (8 × 30 minute modules), a mentoring meeting, a peer observation, and a discussion at a staff meeting focused on *iPLAY* implementation. Completion of these activities will provide each classroom teacher with 14 h of professional learning that is registered with NSW BOSTES. To maintain their accreditation, NSW teachers are required to accumulate 50 h of BOSTES registered professional learning every five years. The project team will provide this professional learning free of charge. The project team will not offer any other compensation to teachers.

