#### Attention control Arm

Teachers in the 10 schools allocated to the attention control arm will be offered teacher professional learning designed to improve their delivery of the NSW Kindergarten–Year 6 Science and Technology curriculum. This program, known as *My Science*, has been shown to increase teacher confidence and student engagement in science [41]. Teachers who complete the *My Science* program will receive 10.5 h of BOSTES-registered teacher professional learning credit. They will also have the option to complete the *iPLAY* program at the end of the study, and earn an additional 14 h of registered professional learning credit.

The primary purpose of employing an attention control intervention is to limit principals’ and teachers’ disappointment at not receiving the *iPLAY* intervention, thereby increasing participation during data collection at the post-intervention and maintenance phases.

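### The trial's economic evaluation asks about value for money against usual practice but takes its incremental cost against the My Science attention control, whose extra cost is then netted off iPLAY's

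*Protocol article*

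**What the plan says.** All of the following is in the Protocol article.

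- **Economic evaluation (cluster trial), comparator.** Value for money is "measured incrementally against the attention control arm". The next sentence says the evaluation will determine "whether the cost of the intervention is justified by the benefits derived from it, measured against usual practice".
- **Same section, costing.** "Costs in each arm of the trial will be estimated from a societal perspective". Then: "The incremental differences in costs will be combined with the behavioral and biophysical outcomes observed in the trial", which gives the incremental cost-effectiveness ratios. The trial-based evaluation is described as "costs and outcomes exactly as per the trial".
- **Same section, model.** The modelled evaluation, which is optional, simulates effects "over the lifetime of the cohort compared with usual practice".
- **Attention control Arm.** Control teachers are offered My Science, a programme for teaching the science and technology curriculum. Those who complete it "will receive 10.5 h of BOSTES-registered teacher professional learning credit". Its stated main purpose is to limit disappointment at not receiving iPLAY and so protect participation at follow-up.
- **Curricular components – classroom teachers.** Completing the iPLAY activities "will provide each classroom teacher with 14 h of professional learning". The same section says teachers need 50 registered hours every five years.

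No section equates the attention control with usual practice, and none removes My Science costs from the control arm.

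**The concern.** A school system deciding whether to adopt iPLAY wants to know what it would cost over and above what schools do now. The control arm is not what schools do now: it is what they do now plus a programme the trial supplies. Differencing the two arms answers a narrower question, namely what iPLAY costs over and above My Science.

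The outcomes in the ratios are behavioural and biophysical. The benefits the article cites for My Science are teacher confidence and student engagement in science, and these do not enter. So the cost of My Science would be credited to iPLAY while its benefit is not counted anywhere.

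This bears on the third hypothesis in Aims and hypotheses, that the intervention is value for money, and on cost-effectiveness as a key secondary outcome in the Abstract. The trial is the only source of comparative cost-effectiveness, because the scale-up study has one arm and its own Economic evaluation section limits it to a description of costs and outcomes. The Abstract's discussion says the results are meant to guide government.

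**Working it through.** The article states no cost figure or cost-effectiveness ratio, so there is no plan figure to reproduce. The check is algebra, followed by a test of whether the documents allow a size.

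**1. What the costing rule delivers.** Let C(i), C(m) and C(u) be the mean cost under iPLAY, My Science and usual practice.

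- Trial-based increment, as written: D(trial) = C(i) − C(m).
- Increment for the question as posed: D(usual) = C(i) − C(u).
- Difference: D(usual) − D(trial) = C(m) − C(u).

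The trial-based increment is too low by exactly what My Science costs above usual practice. With a positive effect E that is the same against either comparator (an assumption, reasonable for fitness if science training does not change it), each ratio is too low by [C(m) − C(u)] / E. If C(m) = C(u), there is no distortion.

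**2. What makes up C(m) − C(u).**

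C(m) − C(u) = My Science programme and delivery cost + value of additional teacher time.

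Additional time per control teacher = h × p × (1 − d), where h is the hours My Science takes, p the proportion of it taken up, and d the share that replaces training teachers would have done anyway.

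**3. Which of these the documents supply.**

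- Programme and delivery cost: not given.
- h: only the 10.5 h of credit is given, with no list of timed activities.
- p: not given.
- d: not given. The accreditation rule averages 50 / 5 = 10 h a year, close to the 10.5 h credit, so substantial displacement is possible but not stated.

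Taking credit as time and full uptake (both assumptions), additional time runs from 10.5 × 1 × (1 − 0) = 10.5 h with no displacement to 10.5 × 1 × (1 − 1) = 0 h with complete displacement. The documents do not narrow that range.

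**4. Whether credit hours measure time.** The iPLAY activities to which the article gives a duration are:

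| Activity | Hours |
|---|---|
| Workshop | 2 |
| Online modules, 8 × 0.5 | 4 |
| Mentor-observed lesson and meeting | 0.5 + 0.5 |
| Peer-observed lesson and discussion | 0.5 + 0.5 |
| Small-group discussion | 0.5 |
| **Total** | **8.5** |

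The credit for this is 14 h. Adding a second peer observation and discussion, with the teacher as observer, gives 8.5 + 1 = 9.5 h. The two observed lessons are ordinary teaching of physical education or sport; without them the total is 8.5 − 1 = 7.5 h. Credit is therefore not a reliable measure of the time an economist would cost, for iPLAY or, by extension, for My Science.

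**Result.** The comparator mismatch is explicit. The direction is fixed provided C(m) exceeds C(u). The size is not determinable.

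**The case against.** **My Science may not cost more than usual practice.** Teachers must accumulate registered training anyway, and 10.5 h is close to the yearly average requirement. If My Science replaces such training, control-arm teacher time is near usual practice and netting it off is right for that component. This stands as a limit on size, and it makes the time component conditional. It does not remove the cost of delivering My Science, and the documents do not say that displacement happens.

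**A ratio against the randomised comparator is coherent.** It is, and it deserves reporting. It is not the question the section poses, which is about usual practice. An attention control may be a fair stand-in for usual practice on fitness, but that does not correct the costs.

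**A full economic plan may set the cost-inclusion rules.** It may. The section defers to pathway analysis, and the scale-up Economic evaluation separates research activity from what adoption would involve, so the team knows the distinction. That separation is stated only for the scale-up study. For the trial, the article states two comparators and a costing rule that follows the trial as run, which is a contradiction and not an omission.

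**The model already names usual practice.** True, and it is optional. The text does not say My Science costs enter it, nor that the comparator cost is reset.

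**A stronger reading to avoid.** A reader might set 14 h against 10.5 h, get 14 − 10.5 = 3.5 h, and infer that three quarters of iPLAY's teacher-time cost is netted away, or go on to a percentage of total cost. The documents do not support either. The hours are credits, uptake and displacement are unknown, and no section gives the share of total cost that is classroom-teacher time.

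**Conclusion.** The point holds as an inconsistency with a known direction and an unknown size. Followed as written, the trial-based ratios do not answer the value-for-money question as posed: they subtract whatever My Science costs above usual practice and so favour iPLAY. The conclusion assumes that My Science adds some cost over usual practice, which is likely for delivery and uncertain for teacher time, and that it does not change the outcomes in the ratios.

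It would be too strong to say that every ratio is known to be biased by a given amount, or that a finding of cost-effectiveness would be an artefact of the control programme. The weight is moderate: the fitness comparison is untouched, and because costs are estimated separately in each arm the problem can be corrected at analysis.

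**What to change.** Before costs are analysed, amend the trial's Economic evaluation section or the economic analysis plan along these lines:

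1. Name usual practice as the single comparator for the value-for-money question.
2. In the base case, leave My Science programme, delivery and additional teacher-time costs out of the control arm, and keep all other measured costs in both arms.
3. State an assumption about how much professional learning is displaced, apply it consistently to iPLAY and My Science time, and vary it in sensitivity analysis.
4. Report the difference against the attention control, as trialled, as a secondary analysis labelled as such.
5. Use the same comparator costs in the Markov model, if it is run.

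This takes a few sentences. It needs no new outcome data or change to the trial, only that My Science costs are recorded as a separate item within the control arm. The price is a ratio likely to be less favourable to iPLAY, and a displacement assumption that has to be defended.
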